#### Pain scale

2.4.3

Pain will be measured using the Visual Analog Scale in the first, fourth, seventh, 10th, 14th, and 17th sessions by a single researcher. In the experimental group, pain will be measured before the administration of phototherapy.

#### Quality of life

2.4.4

The impact of nipple fissures on the quality of life of the participants will be evaluated using the self-administered EQ-5D questionnaire in the third and sixth weeks of the study. The EQ-5D is a generic health-related quality-of-life assessment tool developed in Europe that has been translated and validated in different languages, including Portuguese.^[17]^

### Outcomes

2.5

The main outcomes of the study will be the treatment of nipple fissures and a reduction in nipple pain. The secondary outcomes will be related to the quality of life of the participants.

### Sample size

2.6

The sample size was calculated based on the results of previous studies^[18]^ and considering a possible dropout rate of 10% to 15% throughout the follow-up period. For a 95% confidence interval, 80% test power, and α = 0.05, it was determined that 50 women would be needed for each group (total: 100 participants).

### Statistical analysis

2.7

The statistical analysis will be performed with the aid of SPSS 20.0 (IBM Corporation, Armonk, NY). The Kolmogorov–Smirnov test will be used to determine the normality of the data. Depending on the distribution, the data will be expressed as mean and standard deviation for continuous variables. Repeated-measures analysis will be performed considering group and evaluation time. The Mann–Whitney test, *t* test for independent samples, and Fisher exact test will be used for the comparisons, and a *P* value < .05 will be considered indicative of statistical significance. The statistical analysis will be blinded.

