### Methods

2.1

A controlled clinical trial will be conducted to evaluate the effects of LED therapy on tissue healing, pain, and quality of life in postpartum mothers with nipple fissures. One hundred patients treated at the Mandaqui Hospital in the city of São Paulo, Brazil, with a medical diagnosis of bilateral nipple trauma classified as nipple fissures or cracks will participate in the study. All patients must sign an informed consent form.

All participants will answer a questionnaire addressing basis information (age, gestation time, and infant's age) and history of nipple fissures, will indicate their pain at baseline using the Visual Analog Scale (VAS), and will answer a quality-of-life questionnaire. All participants will sign a statement of informed consent before the onset of the study.

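### The planned group comparisons do not adjust for session-1 fissure length and VAS, which are collected anyway; this costs precision but does not bias the result

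*Protocol article*

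**What the plan says.** Section 2.7 of the protocol article gives the longitudinal analysis in one sentence: "Repeated-measures analysis will be performed considering group and evaluation time". For comparing the groups it lists the Mann–Whitney test and the *t* "test for independent samples, and Fisher exact test will be used for the comparisons". Neither statement names a covariate. On distribution it says "The Kolmogorov–Smirnov test will be used to determine the normality of the data", and the next sentence links distribution to how continuous data are summarised.

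The baseline values are in hand. Under section 2.1, participants "will indicate their pain at baseline using the Visual Analog Scale (VAS"). Section 2.4.3 schedules VAS at six sessions, the first being session 1, and in the experimental group before phototherapy. Section 2.4.2 schedules caliper measurement at seven sessions, again starting with session 1. Section 2.5 makes fissure treatment and less nipple pain the main outcomes. Section 2.6 sets 50 women per group, "considering a possible dropout rate of 10% to 15% throughout the follow-up period".

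**The concern.** Women enter from very different starting points. Section 2.4.2 sorts fissures into three classes, from 3 mm or less to more than 6 mm. Section 2.2 sets a minimum score but no upper limit on fissure size or pain. The starting value is therefore likely to predict later values.

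With 10% to 15% dropout, about 42 to 45 women per arm are evaluable. At that size some chance imbalance at baseline is to be expected, and an unadjusted comparison carries it as noise. What is at stake is a wider confidence interval, and less power, than the same data could give.

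**Working it through.** **Inputs.** From section 2.6: 50 per group, 80% power, α = 0.05 (two-sided assumed), 10% to 15% dropout. From 2.4.2 and 2.4.3: seven caliper and six VAS readings, each including session 1. Assumed, because the documents do not give it: correlation ρ between baseline and follow-up of 0.3, 0.5 or 0.7. The session-1 caliper reading is taken as a baseline; the article states the order relative to phototherapy only for VAS.

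**1. The plan's own figure.** Section 2.6 says "The sample size was calculated based on the results of previous studies" but gives no effect size or SD, so 50 per group cannot be reproduced. It can only be solved backwards, with d = (1.960 + 0.842) × √(2/n):
- n = 50: d = 0.56
- n = 45 (10% dropout): d = 0.59
- n = 42.5 (15% dropout): d = 0.61

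Below, the stated 80% serves only as the starting point.

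**2. Adjusted against final-value comparison.** Baseline adjustment multiplies the variance by 1 − ρ². Power becomes Φ(2.802/√(1 − ρ²) − 1.960). The number per arm for 80% power becomes 50 × (1 − ρ²), rounded up.

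| ρ | 1 − ρ² | variance cut | power | per arm in place of 50 |
|---|---|---|---|---|
| 0.3 | 0.91 | 9% | 83.6% | 46 |
| 0.5 | 0.75 | 25% | 89.9% | 38 |
| 0.7 | 0.51 | 49% | 97.5% | 26 |

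A simulation (2,000 runs per setting, 43 per arm, d = 0.61) gave 83%, 90% and 97% for the adjusted analysis and about 80% for the unadjusted *t* test.

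**3. Adjusted against change-score comparison.** A change score has variance 2(1 − ρ), so the ratio is (1 − ρ²)/[2(1 − ρ)] = (1 + ρ)/2. That is 0.65, 0.75 and 0.85, a cut of 35%, 25% and 15%.

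**4. Baseline as a time level, group main effect tested.** Suppose the effect is the same at every post-baseline reading and is zero at session 1. The group main effect then averages it over all levels, giving 6/7 of it for calipers and 5/6 for VAS. With a common correlation of 0.5 between readings:
- Caliper, main effect: the variance of a woman's mean over seven readings is (1 + 6 × 0.5)/7 = 0.571, so information is (6/7)²/0.571 = 1.29.
- Caliper, adjusted post-baseline mean: variance (1 + 5 × 0.5)/6 − 0.25 = 0.333, so information is 3.00. Relative efficiency is 1.29/3.00 = 0.43.
- VAS, main effect: variance (1 + 5 × 0.5)/6 = 0.583, information (5/6)²/0.583 = 1.19.
- VAS, adjusted: variance (1 + 4 × 0.5)/5 − 0.25 = 0.35, information 2.86. Relative efficiency is 1.19/2.86 = 0.42.

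**5. Main effect or interaction.** The same simulation, with seven readings, a constant effect and equal correlations, gave:

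| ρ | group main effect | group-by-time | adjusted post-baseline mean |
|---|---|---|---|
| 0.3 | 97% | 65% | above 99% |
| 0.5 | 90% | 78% | above 99% |
| 0.7 | 81% | 96% | above 99% |

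Section 2.7 does not say which of the first two tests carries the conclusion, and their power differs widely.

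**The case against.** The strongest reply is that a journal article condenses the plan, and covariates are usual content of an analysis plan that is not shown. That plan may indeed add the covariate. But section 2.7 does not leave the model open: it names the terms and the tests, and a better choice can be judged against what it names.

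A second reply is that baseline is not ignored. This stands for the repeated-measures analysis, where session 1 is itself an evaluation time and a group-by-time comparison uses it. Nor does 2.7 say what the two-sample tests compare; because 2.5 speaks of reduced pain, change scores are a fair reading. Adjustment still gains on either reading (steps 3 to 5), though at ρ = 0.7 the gain over change scores is 15%, not 49%.

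Third, the sizes rest on assumptions. That also stands. If many fissures heal to 0 mm, the late correlation with baseline weakens, so the high-ρ figures are least secure for late fissure length. The efficiency of 0.42 to 0.43 needs equal correlations of 0.5, a constant effect and a main-effect test. That main-effect test still had 81% to 97% power in the simulation.

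**Conclusion.** The point holds as a loss of efficiency. Section 2.7 leaves the session-1 value either unused or used as one more time level, although it is available as a covariate at no extra data cost. For ρ of 0.3 to 0.7, an assumption, the variance saved is 9% to 49% against final values and 35% down to 15% against change scores. The 6/7 and 5/6 dilution applies only if baseline is a time level, the main effect is tested and the effect is constant.

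Three stronger readings are tempting but unsupported:
- **Bias.** Allocation is randomised, so the unadjusted comparison is unbiased. In the simulation its type I error was about 5%.
- **The Kolmogorov–Smirnov check wastes precision.** The text ties that check to data summary; that it selects between *t* and Mann–Whitney is only implied. In a simulation of such a selection rule, power with normal data was 78%, equal to always using *t*. With skewed data it was 94%, against 81% for always *t* and 95% for always Mann–Whitney. Type I error was 5.3% and 5.7%. What remains is narrower: if the check does choose the test, the data decide whether means or ranks are compared, and the choice could differ between sessions.
- **Women with a missing reading are lost.** That follows only from a classical repeated-measures ANOVA. The wording in 2.7 equally covers a mixed model, which keeps them.

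**What to change.** In section 2.7, for each continuous main outcome (fissure length and VAS):
- Analyse the post-baseline readings in one linear mixed model with the session-1 value as covariate, plus group, session and group-by-session, and a within-woman covariance structure named in advance.
- Report the adjusted group difference with its 95% confidence interval at one contrast fixed in advance.
- State that the analysis does not depend on the outcome of a normality check.
- Because fissure length may pile up at 0 mm, where a normal-theory model fits less well, add a rank-based or bootstrap sensitivity analysis.
- State that the session-1 caliper reading is the baseline and when in that session it is taken, as is already done for VAS.

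The cost is wording, settled before outcome data are examined by group. The session-1 readings are already scheduled, so no visit, measurement or participant is added, and SPSS provides mixed models. The price in the analysis is one degree of freedom per covariate and the sensitivity analysis.

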## Discussion

3

This article describes the protocol for a randomized, controlled, clinical trial for the evaluation of the effect of LED therapy for the treatment of nipple fissures in nursing mothers. One of the advantages of the study is the action of LED therapy in the control of nipple pain and the induction of healing of the traumatized breast tissue.^[16]^

Nipple fissures and pain can occur during the lactation period, especially in the initial days of breastfeeding and can even lead to premature weaning. Breast milk is nutritionally ideal for the healthy development of a child and breastfeeding is ideal for orofacial growth and development.^[8,13]^

Nipple pain is generally reported 3 to 6 days after giving birth and can persist for up to 6 weeks.^[1]^ Untreated fissures can compromise the infant's nutrition and can lead to complications, such as mastitis, bleeding, infection, and abscess.^[19]^ The treatments described in the literature include medications, natural extracts, compresses, and lanolin. However, these treatments are not effective with regard to both tissue healing and the control of pain.

Considering the importance of breastfeeding and the high prevalence of nipple fissures, this study proposes a novel way to control nipple pain and accelerate the healing process of nipple fissures through the use of LED therapy, which is a noninvasive technique with no side effects, such as the allergic reactions that can be caused by the ingestion of substances.
